**11. TIME FRAME/DURATION OF THE PROJECT:**

The preparatory work for this study is set to start in January 2012. The LLIN and FSAT interventions will be rolled out at the same time as the baseline cross-sectional study (March 2012/2013). The IRS and larviciding will take place immediately afterwards. Larviciding will be repeated weekly throughout the rainy season (March-July 2012/2013). IRS and LLIN top-up distribution will be repeated 6 months later after the post-transmission season cross-sectional survey (late September 2012/2013). See timeline below.

|  | 2012 | | | | | | | | | | | | 2013 | | | | | | | | | |
| --- | --- | --- | --- | --- | --- | --- | --- | --- | --- | --- | --- | --- | --- | --- | --- | --- | --- | --- | --- | --- | --- | --- |
| Activities | J | F | M | A | M | J | J | A | S | O | N | D | J | F | M | A | M | J | J | A | S | O |
| Community Engagement |  |  |  |  |  |  |  |  |  |  |  |  |  |  |  |  |  |  |  |  |  |  |
| Mapping Study Area |  |  |  |  |  |  |  |  |  |  |  |  |  |  |  |  |  |  |  |  |  |  |
| Updating  Census |  |  |  |  |  |  |  |  |  |  |  |  |  |  |  |  |  |  |  |  |  |  |
| Intervention: FSAT & ITNs |  |  |  |  |  |  |  |  |  |  |  |  |  |  |  |  |  |  |  |  |  |  |
| Intervention: IRS |  |  |  |  |  |  |  |  |  |  |  |  |  |  |  |  |  |  |  |  |  |  |
| Intervention: Larviciding |  |  |  |  |  |  |  |  |  |  |  |  |  |  |  |  |  |  |  |  |  |  |
| Cross-sectional survey |  |  |  |  |  |  |  |  |  |  |  |  |  |  |  |  |  |  |  |  |  |  |

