## *Figure 2. Example of possible layout of hotspots (black blocks) and the surrounding areas (grey blocks) where hotspot targeted interventions will be evaluated). The depicted grid cells are 250x250m.*

## d. Intervention

Up to sixteen clusters will be defined as in the example shown in figure 2. Each cluster consists of a hotspot of malaria transmission and the area surrounding the hotspot 500m in each direction. In the entire study area current malaria control interventions will continue without interruption. In the intervention clusters (i.e. half of the identified hotspots), interventions will be superimposed on ongoing control measures: these intervention hotspots will be targeted with IRS, LLINs, larviciding and FSAT. All the intervention measures will be discussed in more detail in section f. ‘Procedures- Intervention Phase’ however, a brief overview is provided below.

*Indoor Residual Spraying (IRS)*

IRS will be carried out twice per year in all households in the intervention hotspots in the period preceding the long rainy season (March 2012) and six months later (September 2012). Meetings will be held with DOMC to discuss the optimal insecticide for use in the context of ongoing IRS activities in the district.

*Long Lasting Insecticide Treated Bednets (LLIN)*

All compounds in intervention hotspots will be visited in March 2012 and each house will receive a Long Lasting Insecticide Treated Nets for each sleeping space. The DOMC will be consulted about which type of LLINs should be distributed and how best to approach this, but activities will be undertaken by study personnel A follow-up visit is planned one month and 6 months after LLIN distribution to provide additional nets where needed and to monitor accurate use.

*Larviciding*

All mosquito larval habitats in all hotspots and evaluation zones will be mapped using handheld GPS systems in January. All habitats found to persist for more than a week within intervention areas will be treated with a larvicide that has been approved by the Pest Control Product Board and by DOMC, *Bacillus thuringiensis var. israelensis* (Bti) and/or *Bacillus sphaericus* (Bs). Larviciding will begin in March 2012 and continue weekly throughout the rainy season (until July 2012).

*Focal screen and treatment (FSAT)*

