*Indoor residual spraying*

The insecticide that will be used for IRS will be decided on following consultations with DOMC and will be one of the following: lambdacyhalothrin, alphacypermethrin or deltamethrin. Activities and actual spraying will be undertaken by study personnel; IRS will be timed before the peak transmission season in March, at the time-point that is deemed most efficacious by comprehensive malaria transmission models [19] and again after 6 months.

Heads of compounds will be visited by the study team and consent sought. Compounds where the head, or someone with the authority to provide consent, is absent will be visited for a maximum of three times to maximize IRS-coverage in the hotspots. The study team will remove all movable items from the structures that will be sprayed. Any large items that cannot be removed will be moved into the centre of the room and covered with plastic sheets. Sprayers will use protective clothing, masks and gloves and will dispense the insecticide using a back pack sprayer. The walls and roof of all structures in the compound (residential and non-residential) will be sprayed for at least 15 minutes according to guidelines for the insecticide used. The structures will be left locked for 2 hours after which the doors and windows will be opened and allowed to air out for 30 minutes. After this the head of the house may enter to sweep clean. During the government-led IRS program of 2011 lambda-cyhalothrin was used and was reported to occasionally result in itching. Approximately 1 week after the spray households will be revisited to interview members on any reported side effects (see appendix F& H).

Spraying will be repeated at 6-monthly intervals (visits 1 and 3).

*Long-lasting insecticide treated nets distribution*

At the point of the census study staff will document the number of sleeping spaces within each house. At the time of the intervention (March 2012), the study team will distribute one LLIN for each sleeping space within the house, hang the net and explain the proper use and maintenance of the net. All study nets will be labelled for later identification. To avoid potential irritation to the insecticide used in the LLIN, nets will be hung outside for at least 24 hours before being distributed to communities to allow the strength of the insecticide to wane.

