During a second visit, one month after initial LLIN distribution the correct usage of LLINs will be evaluated: the correct hanging of LLINs will be confirmed and household members will be asked to explain how they use the net. If needed, instructions about correct use will be repeated and additional nets can be provided if nets are missing or found to be torn. A third visit will occur to re-assess the quality and use of the nets 6 months after the first visit, in conjunction with the second round of IRS. At this point new ownership and quality will be re-assessed and new nets will be distributed as needed. All information on net use and quality will be recorded (appendix D).

*Focal Screening and Treatment (FSAT)*

Screening of a sentinel population within households

The FSAT utilizes individuals aged 6 month to 20 years as a sentinel group to indicate malaria exposure in the household because this age-group experiences the highest parasite burden [23-24]. For this age group all individuals will be tested for parasites using RDTs regardless of presence of symptoms or not. However clinical care will not be restricted to just this age group. All age groups may experience clinical malaria in our setting ([name] *et al.*, in preparation) and therefore those individuals over 20 years who are found to have fever will also be tested by RDT and receive treatment as oart of the FSAT intervention.

The FSAT campaign will take place in intervention hotspots in March 2012; a second round of FSAT is planned to take place in September 2012. Both campaigns will follow identical procedures.

Screening the sentinel group

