## g. Procedures: evaluation phase

**Community cross-sectional surveys**

*Consent procedure cross-sectional surveys:*

As with the intervention phase, meetings will be organised with the district commissioner, officers and chiefs with the district health team to seek approval for the evaluation phase. Sensitization of communities will be done by chiefs and assistant chiefs and village elders from the study area. Community meetings (barazas) will be held in the selected areas and study staff will explain the purpose of the surveys, the procedures to be followed and the risks and benefits of participation. Information sheets shall be provided in English, DhoLuo, or Kiswahili to all district representatives, chiefs and households (Appendix A).

Households will be informed at the barazas of the timing of the survey and that their compounds may be visited.

On the day of the cross-sectional survey informed consent will be obtained at the individual level. All consent forms will be available in English, DhoLuo, or Kiswahili. Translations will be checked through back-translation (Appendix B). Consent will be obtained by signature or thumb-print accompanied by the signature of an independent witness of selected individuals and/or their parents/guardians. Assent forms will be signed by children between the ages of 13 and 17 years and by their parents/guardians. Each assent form will be accompanied by consent form signed by the parent/guardian.

*Timing of the cross-sectional surveys:*

Six cross-sectional surveys will be conducted (see table in section 11):

- Pre-transmission season (March 2012)
- Peak transmission season (June 2012)
- Post transmission season (September 2012)
- Pre-transmission season (March 2013)
- Peak transmission season (June 2013)
- Post transmission season (September 2013; final survey)

*Procedure cross-sectional surveys:*

Prior to the surveys, census lists for all hotspots will be updated using PDAs, recording the name, age and gender of each household occupant (see appendix C for summary of information collected). For each cross-sectional survey up to 100 individuals above the age of 6 months will be randomly selected from malaria hotspots and up to 500 participants above the age of 6 months will be randomly selected from outside malaria hotspots in each cluster. Randomization will occur at the compound level.

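### The protocol contradicts itself on delivery in 2013, so the exposure compared at the June and September 2013 surveys is undefined

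*Protocol*

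**What the plan says.** **Section 9 (intervention and procedures).** Delivery is dated in 2012 only.
- IRS takes place "in the period preceding the long rainy season (March 2012) and six months later (September 2012". Section 9f adds "Spraying will be repeated at 6-monthly intervals (visits 1 and 3".
- Nets are given out in March 2012, with checks at one and six months.
- For larviciding, section 9d states "Larviciding will begin in March 2012 and continue weekly throughout the rainy season (until July 2012".
- FSAT is done in March 2012, and "a second round of FSAT is planned to take place in September 2012". The sentence that follows refers to the two campaigns as a complete pair.

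**Section 11 (time frame).** The prose repeats the package over two years. Nets and FSAT are rolled out alongside the March survey in 2012/2013, with IRS and larviciding straight after. On larviciding it states "Larviciding will be repeated weekly throughout the rainy season (March-July 2012/2013". On the autumn round it states "IRS and LLIN top-up distribution will be repeated 6 months later after the post-transmission season cross-sectional survey (late September 2012/2013".

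**Sections 9f and 12b (control-area benefits).** Depending on first-year outcomes, and in consultation with the DOMC, the most effective component or components would go to every hotspot in the study area. Sections 9a and 9d say, without qualification, that control areas will not be targeted.

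**Section 9g (surveys).** Six surveys are planned, in March, June and September of 2012 and of 2013. The last is listed as "Post transmission season (September 2013; final survey".

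**The concern.** The abstract describes a two-year cluster-randomised trial, and half of its surveys fall in 2013. A survey estimates the effect of whatever was delivered before it. If the documents do not settle what is delivered in 2013, they do not settle what the second-year comparison estimates.

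A null result in June 2013 would mean failure if a second season of interventions had just been delivered. It would mean ordinary waning if nothing had been delivered since September 2012. It would say little about either if control hotspots had been treated in the meantime. Persistence is a real question here, because the simulation in section 9e predicts an effect that lasts into later years.

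There is also an operational side. FSAT treats whole households, including people without detectable parasites, so field teams need one statement of how many campaigns there are.

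**Working it through.** The protocol gives no figure to reproduce on this point. The check is to set the dates side by side and count months.

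**Inputs.** Delivery dates come from sections 9d, 9f and 11, survey dates from section 9g, and the conditional roll-out from sections 9f and 12b.

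**Step 1: dates by component.**

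| Component | Section 9 | Section 11 (prose) |
|---|---|---|
| IRS | March and September 2012 | After the March survey and in late September, 2012 and 2013 |
| Nets | March 2012, checks at 1 and 6 months | March and late-September top-up, 2012 and 2013 |
| Larviciding | March to July 2012 | March to July, 2012 and 2013 |
| FSAT | March and September 2012 | March 2012 and March 2013 |

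The prose of section 11 names no September FSAT round. It refers to a timeline grid whose shading is not legible in the copy reviewed, so nothing is concluded from that.

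**Step 2: months from last delivery to each 2013 survey.** Number the months from January 2012 = 1. Then July 2012 = 7, September 2012 = 9, March 2013 = 15, June 2013 = 18, July 2013 = 19 and September 2013 = 21. Elapsed time is the survey month minus the delivery month.

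| Survey | Section 9 dates | Section 11 dates |
|---|---|---|
| March 2013 | IRS/FSAT 15 − 9 = 6; larviciding 15 − 7 = 8 | Same earlier delivery; the new round coincides with or follows the survey |
| June 2013 | IRS/FSAT 18 − 9 = 9; larviciding 18 − 7 = 11 | March 2013 round 18 − 15 = 3; larviciding in progress |
| September 2013 | IRS/FSAT 21 − 9 = 12; larviciding 21 − 7 = 14 | March 2013 round 21 − 15 = 6; larviciding 21 − 19 = 2 |

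The protocol gives months only. Assuming mid-month surveys and a round on 25 September 2012, the intervals after that round are 5.6, 8.6 and 11.7 months. These agree with the whole-month counts of 6, 9 and 12.

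**Step 3: which surveys differ.** In March 2013 the two dated calendars agree on what has already been delivered. They part in June and September 2013, which is two of six surveys: the only peak-season survey of the second year, and the final one.

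**Step 4: the third account.** Under the conditional roll-out, control hotspots could receive some or all of the package after the first year. The June and September 2013 comparison would then have no untargeted control hotspots, whichever dated calendar applied to the intervention arm. No date is given for that roll-out relative to any 2013 survey.

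**The case against.** The best defence is that section 9 gives first-year detail and section 11 gives the project calendar. No passage says that delivery stops after September 2012. Section 9d describes IRS as twice yearly, section 9f speaks of a first round and a first year, the abstract says two years, and the budget is annual. The visit numbers for spraying could belong to a cycle within one year. The March–May 2012 timing in section 9f describes the first round only.

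Part of this stands. For IRS and nets, section 9 can be read as silent about 2013. It does not remove the conflict. The FSAT text counts two campaigns, March and September 2012, whereas section 11 has an FSAT roll-out in March 2013. Section 9d gives larviciding an end date in July 2012. If year two was meant to be conditional, as sections 9f and 12b suggest, the unconditional 2013 dates in section 11 are themselves wrong.

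A reader might infer more than the documents support:
- **All three 2013 surveys are compromised.** Under the dated calendars, March 2013 is not.
- **Section 11 drops the September FSAT round.** Only its prose can be read; the grid may have shown the round.
- **2012 and 2013 results will be averaged.** Section 10b does not say so, and the handling of repeated surveys may be set in an analysis plan that is not shown.
- **The late-September 2013 round is a flaw because it follows the final survey.** It biases no outcome. At most, it lies outside the evaluated intervention, and it exists only under section 11.

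**Conclusion.** The contradiction is real and concerns what is delivered, not merely how it is described. Three accounts of 2013 stand in the protocol: delivery dated in 2012 only, a repeat in 2013, and a roll-out to all hotspots that depends on results. They give the June and September 2013 surveys three different meanings: persistence at 9 and 12 months after the last IRS and FSAT round, sustained delivery, or a comparison without untargeted control hotspots.

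The effect is limited to those two of six surveys. The June and September 2012 results do not depend on how the conflict is resolved.

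This rests on two assumptions: that the September 2012 FSAT round in section 9 belongs to both calendars, and that any roll-out to control hotspots would not precede the March 2013 survey. If roll-out came sooner, March 2013 would also be affected.

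**What to change.** Reconcile sections 9d, 9f, 11 and 12b into one dated calendar for each component and each arm. Which schedule it should contain is for the investigators and the DOMC; this review takes no position.

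In the same revision:
- State whether and when any roll-out to control hotspots can occur relative to the March, June and September 2013 surveys.
- State which question the June and September 2013 surveys answer under that calendar: sustained delivery, or persistence after delivery ends.
- Treat those surveys as part of the randomised comparison only while control hotspots remain untargeted.
- If a round after the final survey is kept, note that it falls outside the evaluated intervention.

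This costs protocol wording and one corrected timetable, with no extra surveys or participants. The possible price is a narrower statement of what the 2013 surveys can conclude.

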**12. ETHICAL CONSIDERATIONS:**

a. Consent

Participation in the study is fully voluntary and participants have the right to refuse at any time during the study. Consent will be obtained in the preferred local language, DhoLuo, Kiswahili, or English directly from all adults participating in the cross-sectional survey. For children less than18 years of age, consent will be obtained from parents or guardians. In addition, child assent will be obtained for children who are greater than 13 but less than 18 years and live with a parent or guardian. Children providing assent will be asked to sign next to their name on the assent form. As defined in the Kenya national guidelines for HIV counselling and testing, Kenyan subjects between 13 and 17 years of age who are pregnant, are married, head of a household, or a parent are considered “mature minors” and are able to consent for themselves [31]. Mature minors will be consented directly (therefore assent will not be sought). The consent and assent forms are given in Appendix B. The reading level of the consent form is 8.5. Data from the demographic surveillance system (DSS) in Nyanza Province showed that approximately 77% of mothers had primary school education [32] which is approximately equivalent to the 8th grade in the US.

During the consenting process, the study will be explained and the consent form will be read to each person. It will be emphasised that participation is voluntary. The consent form will detail the design of the study, the questionnaires, the finger prick, and the blood samples taken. If participants agree, they will be asked to sign the consent or assent form. The storage of the blood samples will then be explained to each person. Everyone will have the option to consent to have their blood samples stored at KEMRI/CDC, and/or to consent for part of the analyses to be conducted outside Kenya. Samples will be stored for 5 years to adhere to Good Clinical Practice guidelines. All persons will be provided with a copy of the blank consent form for their records after they have agreed to participate in the study.

b. Benefits to intervention participants

*Benefits to participants in intervention area*

Intervention participants will receive intensive malaria control for their household: IRS, LLINs, larviciding and in FSAT. These interventions are expected to have a direct and an indirect beneficial effect on the level of malaria the household is exposed to: IRS will reduce indoor mosquito exposure, LLINs will protect individuals from (infected) mosquito bites, larviciding will reduce indoor and outdoor mosquito exposure; FSAT will clear parasite carriage and provide 3-4 weeks of efficacious prophylaxis against malaria infections. These interventions are provided free of charge.

The wider community, i.e. those living in the vicinity of hotspots will not receive any direct benefits from the interventions, but are likely to experience indirect effects. Reductions in neighbouring areas with high malaria prevalence may result in reduced malaria transmission in the wider region.

*Benefits to participants in control area*

Participants in the control areas will not benefit from the interventions in the short term but will benefit from free screening and treatment for symptomatic malaria. However, the information that will be learned as a result of this study can benefit them in the future through more effective and targeted malaria control interventions and the possible overall reduction in malaria transmission that may ensue. There are plans for district-wide government-led interventions such as IRS to take place. All these will continue as planned and none will be withheld from the communities. Depending on the outcomes of the first year of the intervention, in consultation with the DOMC, to roll-out the most efficacious intervention/s to all hotspots in the study area.

*Community benefits*

The community benefit of the project is that we expect malaria transmission in the entire area to be reduced as a result of our hotspot targeted interventions. Free LLINs and intensive vector controlled will be offered to individuals residing in some of the strongholds of malaria transmission in Rachuonyo district; plausibly leading to a direct benefit to this part of the population that is most affected by malaria. The MOH is also expected to benefit from this study by gaining a lot of information on the status of malaria transmission in this area of Rachuonyo district as the findings will be shared with them. The Government of Kenya may also benefit by improving malaria control strategies and targeting efforts where they can be most effective.

c. Risks to intervention participants

None of the interventions that are proposed in this study are experimental. LLINs and IRS are part of the malaria control efforts by the DOMC for the district; larviciding has been done in districts bordering or close to Rachuonyo district, in Nyando, Kisii, Suba and Kakamega districts [22]. All insecticides used will have been approved by DOMC and PCPB prior to application. The FSAT approach to screen asymptomatic children and treat all inhabitants of households where ≥1 individual is found parasite positive by RDT has not been done routinely in Kenya but is an extension of screening and treatment of asymptomatic individuals that is proposed under the Kenyan National Malaria Strategy for 2009-2017[[13](#_ENREF_13)]. The national strategy does not currently propose to treat household members of asymptomatic parasite carriers; the approach is justified by evidence of clustering of parasite carriage at household level [2, 6, 25, 33] and the low sensitivity of RDTs for detecting all epidemiologically relevant parasite densities [[14](#_ENREF_14)]. We will provide supervised treatment with the first line antimalarial drug AL that has an excellent safety profile and is recommended for treatment of symptomatic and asymptomatic malaria infections in Kenya [[13](#_ENREF_13)]. We will also closely monitor and document any reported side effects of all interventions by questionnaires on all days of treatment and one week after treatment, IRS and ITN distribution.

d. Benefits to survey participants

All participants of the cross-sectional survey will benefit from knowing their haemoglobin level and whether they have a clinical malaria infection. Any participant with low haemoglobin will receive treatment for anaemia. All individuals who are diagnosed with a clinical malaria episode will be treated with AL according to Kenya national guidelines.

e. Risks to survey participants

This survey is of minimal risk to participants. Blood will be collected by fingerprick only using a sterile lancet, and the total amount of blood collected is very small (200-300μl); participants may experience only a small bruise at the site where we collect the blood. Blood draws will be carried out by trained medical or laboratory staff members to ensure these are done in as safe a manner as possible.

After screening, each person who is diagnosed with clinical malaria will be treated with first line malaria treatment recommended by the Ministry of Health, Kenya, AL. AL is considered a very safe drug except in pregnant women (where there may be possible risk to the developing foetus) and very young children (where safety data to support its use are not available).

To minimize drug exposure in these risk groups, children under 6 months of age will be excluded from the study, and pregnant women will receive alternative medication as outlined above.

We will take steps to ensure that each study participant’s personal information will be protected. All questionnaires will be labelled with the participant name and person ID. Filter paper samples and other samples will be labelled using a personal ID only, which will only be known to study staff. After the questionnaires are completed, they will be returned to the data management staff while the filter paper samples will be returned to the laboratory staff at KEMRI/CDC in Kisian. Once at the laboratory, only data management staff will possess the link between the laboratory samples and the participants’ identifiable information.

